**Methods:**

We implemented a novel model called the “Developmental and Sequenced One-to-One Educational Intervention” (DS1-EI) in 5- to 9-year-old children with co-occurring ASD and ID. The treatment protocol was adapted for school implementation by designing it using an educational agenda. The intervention was based on intensity, regular assessments, updating objectives, encouraging spontaneous communication, promoting skills through play with peers, supporting positive behaviors, providing supervision, capitalizing on teachers’ unique skills, and providing developmental and sequenced learning. Developmental learning implies that the focus of training is what is close to the developmental expectations given a child’s development in a specific domain. Sequenced learning means that the teacher changes the learning activities every 10–15 min to maintain the child’s attention in the context of an anticipated time agenda. We selected 11 French institutions in which we implemented the model in small classrooms. Each institution recruited participants per dyads matched by age, sex, and developmental quotient. Patients from each dyad were then randomized to a DS1-EI group or a Treatment as usual (TAU) group for 36 months. The primary variables – the Childhood Autism Rating scale (CARS) and the psychoeducational profile (PEP-3) – will be blindly assessed by independent raters at the 18-month and 36-month follow-up.

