**Figure 1 F1:**
[figure not shown]
**Institutions and participants’ enrollment in the DS1-EI trial by site**. HDJ, *Hopital de Jour* (Day care medical center); IME, *Institut Medico-Educatif* (Special education center).

Each parent provided informed written consent before inclusion. The inclusion criteria were a current diagnosis of ASD confirmed by a clinical assessment based on the International Classification of Diseases, 10th edition criteria and the Autism Diagnostic Interview-Revised (ADI-R) (36); an intellectual handicap with financial compensation from local agencies [*Maison Départementale du Handicap* (MDPH)]; being aged between 5 and 9 years; and having a communication developmental age of 24 months and under based on a Vineland assessment or a 3-year speech delay based on a Psycho-Educational Profile, third edition. We did not exclude children with known organic syndromes and/or non-stabilized neuropaediatric (e.g., seizures) or medical (e.g., diabetes mellitus) comorbidities. However, during the medical assessment, we specifically listed comorbidities. The exclusion criteria were limited to parents’ refusal to participate; family’s plans to change institutions in the short term for any reason; and patient’s severe behavioral impairments that would challenge treatment adherence. Of note, this last exclusion criterion was based on local institution staff decision. Before randomization, each site was requested to assess the IQ of the participants based on the Kaufman Assessment Battery for Children second edition (KABC-II) or, failing that, Vineland scores. Based on these results, dyads of participants matched for sex, age, and developmental quotient (DQ) were formed to limit the risk of bias between groups. Randomization before group allocation to TAU or DS1-EI group was performed by drawing lots in each dyad per site so that each site could have a TAU group and a DS1-EI group of three to four participants each. Randomization was performed by the methodological coordinating team at the Salpêtrière Hospital and was independent from local inclusion sites. TAU was defined as all therapeutic interventions given to a specific child. Given the study duration, we did not recommend not to change children’s therapeutic protocol in the TAU group during the study period. The trial duration was defined as 36 months but included 12-, 18-, and 24-month intermediate assessments.

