### Primary and Secondary Variables

Table 3 summarizes the variables that we planned to measure at enrollment and at several time points throughout the trial. The primary outcome variables were (i) the Childhood Autism Rating scale (CARS), which measures autism severity (38); (ii) the psychoeducational profile, third edition (PEP-3), which measures the total DQ and 5-dimensional DQs related to cognition, receptive language, expressive language, fine motor skills, gross motor skills, and imitation, and (iii) the school’s assessment (39). Secondary variables included the following measures: (i) the *Vineland Adaptive Behavior Scale II* (VABS-II) as a behavioral scale of independence; this scale is assessed through a parent/educator interview and is used to assess the ability of children to perform the daily activities required for personal and social sufficiency. The VABS-II examines four specific domains: Communication, Daily Living Skills, Socialization, and Motor Skills. The subscale scores are totaled to yield an Adaptive Behavior Composite score (40). (ii) The KABC-II standardized neuropsychological assessment to measure intelligence skills. This battery measures Verbal, Performance, Working Memory, Processing Speed and Total quotients (41). (iii) The *Clinical Global Impression* (CGI), which was used to assess global severity (42). (iv) Finally, the *Children Global Assessment Scale* (CGAS) (43). To assess clinical change during the 36-month study, we used a single-blind procedure (independent raters were blind to study group allocation) for all clinical assessments (PEP-3, KABC-II, CARS). Blind assessment was not possible for the measures that required 2-week observations of the participants (CGI, CGAS, school tests) or a parental interview (ADI-R, VABS-II).

**Table 3 T3:** **DS1-EI study procedure and evaluation criteria**.

	Selection	Inclusion	M12	M18	M24	M36
Inclusion criteria	X	–	–	–	–	–
Informed consent	X	–	–	–	–	–
CIM-10 diagnosis	–	X	–	X	–	X
Comorbidity	–	X	–	X	–	X
ADI-R	–	X	–	X	–	X
Vineland	–	X	X	X	X	X
CARS	–	X	–	X	–	X
CGAS	–	X	X	X	–	X
CGI	–	X	X	X	–	X
KABC	–	X	–	X	–	X
PEP-III	–	X	–	X	–	X
School assessment	–	X	X	X	X	X

*ADI-R, Autism Diagnostic Interview-Revised; CARS, Childhood Autism Rating Scale; CGI, Clinical Global Impression; CGAS, Clinical Global Assessment Score; PEP-3, Psychoeducational Profile, 3rd Edition; DQ, developmental quotient; KABC, Kaufmann Assessment Battery for Children*.

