### Number of Participants

From previous studies that showed significant results in terms of efficacy it appears that the minimal number of patients in parallel design was 50 (2). This was the case for behavioral ABA approach [e.g., Ref. (6)] or for developmental ESDM approach [e.g., Ref. (3)]. The number of patients to enroll was based on the following theoretical statistics estimation: for a moderate effect size (α = 0.6), a power fixed at 80%, and a level of significance for a *p*-value fixed at <0.05, 80 patients randomized into two groups are required for a student *t*-test. Given our choice to use linear mixed models (see below) to take into account participant’s effect, we planned to recruit from 70 to 80 participants.

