## Discussion

We hope that the current trial will help demonstrate the feasibility of adapting and task-shifting a group of interventions used primarily as early interventions for autism to a school-based context and for use with older individuals with autism and intellectual disabilities. The school-based intervention program [the developmental and sequenced one-to-one educational intervention (DS1-EI)] was adapted from several methods including TEACCH (4, 5), ESDM (3), and ABA (6, 37). The key principles of the method are the intensity, the regular assessments and updating of objectives, the encouragement of spontaneous communication, promotion of skills through play with peers, support of positive behaviors instead of tackling challenging behaviors, regular team supervision, capitalization on teachers’ unique skills, and developmental and sequenced learning (2). The use of sequenced learning (i.e., teacher and activity change every 10–15 min to keep the child’s attention in the context of an anticipated time agenda) is likely the most original proposal. We are aware that treating children with autism and ID is very challenging. The effect sizes are typically small. To balance this risk of failure, we chose to have a rather long study duration with two single-blind assessments at 18 and 36 months. Given the number of sites, which may have introduced bias, we are satisfied that we did not find differences between the groups at baseline.

We are aware that there are several limitations to this trial. First, given the severity of the patients’ conditions, the study duration and the nature of the intervention, only a single-blind for the primary variables was feasible. Second, the method used to randomize participants (to limit the bias of TAU) combined with the study duration and the supervision of local teams is likely to modify local staff practice and to lead to some DS1-EI principles being used in the TAU group as well. Third, because our public sponsors required us to balance hospital/academic/large city sites and non-hospital/remote rural area sites, we cannot assume that we will achieve a uniform level of adherence to the program from one site to another. Finally, given the study duration, we do not know whether we will retain a sufficient number of patients in the program to maintain the statistical power needed for per protocol analyses.

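### The primary outcome set is unranked and differs between sections, and no score, model term or visit is named as the one that decides the trial

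*Protocol article*

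**What the plan says.** **Primary and Secondary Variables** gives a numbered list. It opens "The primary outcome variables were (i) the Childhood Autism Rating scale (CARS), which measures autism severity (38", continues with the PEP-3, "which measures the total DQ and 5-dimensional DQs related to cognition, receptive language, expressive language, fine motor skills, gross motor skills, and imitation", and closes "and (iii) the school’s assessment (39". No order of importance is given. The text counts five PEP-3 dimensions but names six, and Table 4 reports six. The same section says that school tests, which need two weeks of observation, could not be assessed blind.

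**Abstract, Methods** names only CARS and PEP-3 as the primary variables and says they "will be blindly assessed by independent raters at the 18-month and 36-month follow-up".

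**Discussion** describes "two single-blind assessments at 18 and 36 months" and, in its first limitation, treats the primary variables as single-blind.

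**Participants and Recruitment** (text after Figure 1) states: "The trial duration was defined as 36 months but included 12-, 18-, and 24-month intermediate assessments".

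**Number of Participants** sizes the trial for a Student t-test with a standardised effect of 0.6, 80% power and "a level of significance for a *p*-value fixed at <0.05". This is the only significance level in the document.

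**Statistical Analysis** fits one linear mixed model per variable, primary or secondary, with group, time (baseline, 18 and 36 months) and their interaction. It does not say which term or visit carries the primary conclusion.

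**The concern.** Which outcome decides the trial, and when, is a choice that belongs in the protocol. Here the choice is made but not finished. The Methods give three instruments and the Abstract two; one instrument yields a total and six domain scores; two follow-up visits are reported side by side; and a model with several terms is applied to all of them alike. The sample size, by contrast, assumes one comparison.

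Two things are at stake. First, if a favourable result on any of these scores may be reported as a positive primary finding, the 5% level used to size the trial no longer describes the error rate, and the score or visit can be picked after the data are seen. Second, if the school assessment is primary, an unblinded measure could carry the main claim of a trial that presents its primary variables as single-blind.

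**Working it through.** **1. Is the primary set consistent?**

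| Section | Primary variables | Blinding |
|---|---|---|
| Abstract, Methods | CARS, PEP-3 | blind, independent raters |
| Primary and Secondary Variables | CARS, PEP-3, school assessment | CARS and PEP-3 blind; school tests not |
| Discussion | not listed | primary variables single-blind |

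The Abstract and Discussion agree with each other only if the school assessment is not primary. The Methods list says that it is.

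**2. How many scores could be primary?** Two instruments (Abstract) or three (Methods). If each PEP-3 score counts and the school assessment is taken as one score (the number is not given): 1 (CARS) + 1 (PEP-3 total) + 6 (domains) + 1 (school) = 9. If 18 and 36 months are tested separately: 9 × 2 = 18.

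**3. The plan's own sample size.** Effect 0.6, two-sided 0.05 and 80% power need 88 patients by the normal formula and 90 by the exact t-test; one-sided they need 70 and 72. The stated 80 is not reproduced. That is a separate matter and does not decide this point. With the 75 enrolled, a single two-sided t-test at 0.05 has 72.7% power at effect 0.6; with 80 patients, 75.5%.

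**4. If any one primary suffices at 0.05.** For k independent tests, the chance of at least one false positive is 1 − 0.95^k. For equally correlated tests (multivariate normal, common correlation r) the chance is lower. The document gives no correlations, so r is an assumption.

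| Tests | k | r = 0 | r = 0.5 | r = 0.9 |
|---|---|---|---|---|
| Two instruments, one time | 2 | 9.75% | 9.1% | about 7% |
| Three instruments, one time | 3 | 14.3% | 12.5% | 8.4% |
| Nine scores, one time | 9 | 37.0% | 27% | 12.4% |
| Nine scores, two times | 18 | 60.3% | 40% | 15% |

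The last row uses one common correlation for all 18 tests. With the between-visit correlation held at 0.5 or 0.7 and the between-score correlation at 0.9, it gives about 20–21% instead of 15%.

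**5. If all primaries must succeed.** The chance that all are falsely positive cannot exceed 5%, so there is no inflation. The cost is power. With 75 patients, effect 0.6 on every outcome and independent tests, power is 0.727² = 0.53 for two instruments and 0.727³ = 0.38 for three. Positive correlation raises these towards, but not above, 0.727.

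**6. Cost of splitting alpha.** Holm across two outcomes tests the smaller p-value at 0.05/2 = 0.025. A single test at that level with 75 patients has 62.2% power at effect 0.6, against 72.7% at 0.05.

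**The case against.** The strongest reply is that much of the alarm depends on rules the document does not state, and several parts of that reply stand.

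- A reader might infer that every primary score is to be tested at p<0.05. The level appears only as an input to the sample size; Statistical Analysis sets none.
- A reader might infer separate primary tests at 18 and 36 months. The plan is one model per variable, and group × time could be one joint test. Participants and Recruitment calls the 18-month visit intermediate. Eighteen tests is therefore an upper reading, not the plan as written.
- A reader might take nine scores as the minimum. The PEP-3 wording may only describe what the instrument yields, much as the same section describes the VABS-II and KABC-II. On the document's own lists the minimum is two or three.
- A false-positive rate far above 5% presupposes that any one success is enough. The document states neither that rule nor its opposite.
- A multiplicity method may sit in an analysis plan that is not shown, so its absence here is not a finding.

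What the reply does not remove is the primary set itself. The article declares it, ranks nothing in it, miscounts the PEP-3 domains, and contradicts itself on whether an unblinded measure belongs to it. A later adjustment method would not settle which of the two lists is right.

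**Conclusion.** The point holds as a defect of definition. The primary set is unranked and inconsistent between the Abstract, Methods and Discussion; no decisive score, model term or visit is named; and the sample size is for one test.

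The size depends on a success rule the document leaves open. If any one primary suffices at two-sided 0.05, the false-positive chance at a single time is about 7–10% for two instruments, 8–14% for three and 12–37% for nine scores, over assumed correlations of 0.9 to 0. Counting both visits separately gives 15–60%, as an upper reading only. If all must succeed, the 5% level holds but power falls below the single-test 73%. Under neither rule does the single-test calculation describe the design. The documents do not support saying that the trial's error rate is far above 5% as a fact; they support saying that nothing in this text keeps it at 5%.

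**What to change.** Before outcome data are unblinded:

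1. Name one ordered primary family at 36 months and the model contrast that tests it. For example, test the group difference in CARS change at 0.05, then PEP-3 total DQ at 0.05 only if CARS is significant. Nothing in the document ranks CARS above PEP-3, so the sponsor may choose the order, or use Holm across the two.
2. Make the PEP-3 domain scores, the 18-month contrasts and the unblinded school assessment secondary.
3. Align the Abstract, Primary and Secondary Variables and the Discussion with that set, and correct the PEP-3 count from five dimensions to six.

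**Cost.** No extra patients are needed for the change itself. It does need a protocol amendment and a registry update, because moving the school assessment out of the Methods list changes an approved and registered protocol with 75 children already enrolled. A fixed sequence costs the first test nothing, but the second can be claimed only if the first succeeds. With Holm, the first step at 0.025 lowers power at effect 0.6 with 75 patients from about 73% to about 62%.

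### The article gives two different primary outcome sets: Methods includes the unblinded school assessment, while the abstract omits it and the Discussion calls the primary variables single-blind

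*Protocol article*

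**What the plan says.** Three places in the protocol article describe the primary outcomes.

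- **Primary and Secondary Variables.** The list of primary variables has CARS, then PEP-3, "and (iii) the school’s assessment". Later in the same paragraph the single-blind procedure is said to apply "for all clinical assessments (PEP-3, KABC-II, CARS"), and the school measure is placed among those rated open: "Blind assessment was not possible for the measures that required 2-week observations of the participants (CGI, CGAS, school tests").
- **Abstract, Methods.** The primary variables are given as "the Childhood Autism Rating scale (CARS) and the psychoeducational profile (PEP-3") and nothing else. These "will be blindly assessed by independent raters at the 18-month and 36-month follow-up".
- **Discussion, limitations.** The article says that "only a single-blind for the primary variables was feasible", with no exception for any primary variable.

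Table 3 schedules the school assessment alongside the other measures but does not mark any measure as primary or secondary. The Statistical Analysis section applies the same linear mixed model to primary and secondary variables alike and puts the primaries in no order.

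**The concern.** Which outcomes are primary determines which result counts as the trial's answer. Here a reader of the abstract and a reader of Methods would name different sets, and the difference is the one measure that is not blinded. If CARS and PEP-3 were flat and the school assessment favoured DS1-EI, the Methods list would allow a positive primary finding. A reader relying on the abstract or the Discussion would take that finding to come from blinded ratings.

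The risk from open rating is plausible in this design. Children were randomised within site, so the allocation is likely to be known locally. The article itself ties the lack of blinding to a two-week observation of the child. The arms also differ in time spent at school, so raters of a school measure may have seen more of some children than of others. The article does not say who rates the measure or under what conditions, so this last point is a possibility and not a stated fact.

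**Working it through.** **Step 1. Compare the three statements.**

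| Place | Primary set | Blinding stated |
|---|---|---|
| Abstract, Methods | CARS, PEP-3 | Both blind |
| Primary and Secondary Variables | CARS, PEP-3, school assessment | CARS and PEP-3 blind; school tests not blind |
| Discussion, limitations | Primary variables, not listed | Single-blind, no exception |

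The abstract and Methods agree on CARS and PEP-3 and on their blinding. They disagree on whether a third primary exists. The Discussion's statement is true of the abstract's set (two of two blinded) and untrue of the Methods set (two of three blinded).

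**Step 2. Look for anything in the article that settles it.** Table 3 does not label primaries. The Statistical Analysis section neither ranks them nor says what happens if they disagree. The Number of Participants section bases its calculation on an effect size of 0.6 without naming the outcome. Nothing shown decides between the two sets.

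**Step 3. Is there a figure in the plan to reproduce?** None bears on this point. The sample size of 80 is a separate matter and is not used below.

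**Step 4. Illustrate what an open-rating bias could do.** The bias sizes are assumptions; the article gives none.

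Inputs: 38 and 37 children (abstract); significance level 0.05 (Number of Participants), taken as two-sided because sidedness is not stated; no true effect; a rating bias of b standard deviations between arms; a two-sample t-test.

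- Noncentrality = b × √(38 × 37 / 75) = b × √18.75 = b × 4.33, with 38 + 37 − 2 = 73 degrees of freedom.
- False-positive probability = the chance that a noncentral t with that noncentrality exceeds the two-sided 5% critical value in absolute size.

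| Assumed bias b (SD) | Noncentrality | Rejection on the school assessment |
|---|---|---|
| 0 | 0 | 5.0% |
| 0.1 | 0.43 | 7.1% |
| 0.2 | 0.87 | 13.7% |
| 0.3 | 1.30 | 24.9% |
| 0.4 | 1.73 | 40.1% |
| 0.5 | 2.16 | 57.0% |

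The plan uses a mixed model with a group-by-time interaction, not this t-test, so the table shows only how quickly the error rate rises with bias. It does not estimate the error rate of this trial.

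**The case against.** The strongest reply is that nothing is hidden. Methods declares the school tests unblinded in the same paragraph that makes them primary. The abstract is accurate for the two measures it names; its fault is only that it leaves out the third. The Discussion sentence sits in a list of limitations and concedes weak blinding rather than boasting of strong blinding. In a school-based educational trial, a school outcome is also a defensible primary, and CARS and PEP-3 are blinded wherever their blinding is described. All of this stands. It shows that the fault is inconsistency and not concealment, but it does not make the two lists agree. A fuller analysis plan might rank the outcomes, but it cannot reconcile two definitions already in print.

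A reader might infer more than the article supports:

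- **That the school content is taught in one arm only.** TAU children had 3.4 h/week of school on average, the curriculum is adapted from the national programme, and the Discussion expects some DS1-EI principles to reach the TAU group.
- **That the school assessment is built on the DS1-EI curriculum.** The article says the intervention's objectives follow national school recommendations. It does not describe the content of the outcome instrument, so alignment is an inference.
- **That the gap in school hours shows measurement bias.** The 6.0 h/week difference (9.4 − 3.4) largely reflects the assigned intervention. It makes unequal observation possible but does not demonstrate it.
- **That a false-positive rate of 25% or 57% is to be expected.** Those values follow from assumed biases of 0.3 and 0.5 SD. At 0.1 SD the rate is 7.1%.

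**Conclusion.** Wrong as written. The article contains two primary outcome sets, and the Discussion's description of blinding does not fit the set given in Methods. Under the Methods list one of three primaries is open-rated, and nothing shown prevents a primary efficacy conclusion from resting on it.

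The contradiction needs no assumption; it is in the text. The consequence is a risk of unknown size, because the article gives no information on bias, on the instrument's content or on who rates it. The range of about 7% to 57% is conditional on an assumed bias of 0.1 to 0.5 SD, no true effect, and a simple two-sided t-test with 38 against 37. The article also does not show which set was intended, so it cannot be said from this text alone that Methods is wrong and the abstract right.

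**What to change.** Before outcome analysis, use one primary set in the abstract, the Primary and Secondary Variables section and the Discussion, and state for each measure whether it is rated blind.

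The simplest choice is the set the abstract already gives: CARS and PEP-3 primary, with the school assessment moved to the secondary variables and labelled unblinded. Check this against the full protocol first. If that shows the school assessment was meant to be primary, keep it, say that it is unblinded wherever the primaries are described, and state that the primary conclusion will not rest on it alone.

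The text change is a few lines and no data are lost. The cost is one fewer primary outcome. Because all 75 children were already enrolled and baseline data are reported, the change must be dated and justified so that it is not taken for a choice made after seeing results.
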